##### Implementation

As per Proctor et al [43], the following digital health implementation outcomes will be measured: clinician acceptability, feasibility, and appropriateness using validated items sent to clinicians via a hyperlink to an online survey. Parent acceptability will be assessed using the same validated items embedded within the above-mentioned computer-assisted telephone interviewing or online survey.

##### Maintenance

The parental opt-out rates from HB4HNEKids for intervention and control will be assessed via project and electronic health service records used to deliver the program as per the primary outcome – reach. Characteristics of parents opting out of receiving HB4HNEKids in both groups will also be assessed at 18 months post baby’s birth.

#### Sample Size and Power Calculation

For the primary outcome, a sample of 1126 participants or families per trial arm will enable a detectable difference of 9.8%, assuming the opt-in model will achieve approximately 65% reach at 18 months (based on previous pilot data [awaiting publication]) with 80% power, α of .05, and an intraclass correlation coefficient of 0.05. Given the sectors involved in the trial are estimated to account for 55% of births within the Hunter New England area, achieving this sample should be possible.

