Healthy Beginnings for Hunter New England Kids (HB4HNEKids) is an innovative SMS text message (mHealth) program designed to be delivered alongside the usual CFHS. It provides age-and-stage relevant preventative health information, child health check and immunization reminders, as well as information on health screening and support services, directly to parents during the first 2000 days (commencing within days after birth up until 5 years). HB4HNEKids was adapted from an original efficacy trial demonstrating improvements in infant feeding practices and screen time [22], and a pilot effectiveness trial which evaluated its feasibility, acceptability, and effectiveness when embedded into routine health service delivery within 5 diverse CFHS in the Hunter New England region of New South Wales. The pilot trial, implementing HB4HNEKids into routine health service delivery demonstrated that HB4HNEKids digital model of care program was feasibly delivered to families (delivered to over 6000 parents), reached approximately 70% (6243/8501) of eligible parents at a relatively low cost (approximately Aus $4.66/family per year, equivalent to US $3.03/family per year), had high parental engagement (73/96, 76% of parents or carers reported reading the messages) and acceptability (89/96, 93% of parents liked the program) [23]. The pilot also indicated that HB4HNEKids participants had improved child vegetable intakes (*P*=.006) and parental mental well-being (*P*<.001) at 12 months compared with families who had not received the program [24]. In addition, breastfeeding rates were 5% higher in the HB4HNEKids participants at 6 and 12 months compared with families who had not received the intervention. Thus, while the pilot of the HB4HNEKids program demonstrates promise for population-wide scale-up, the optimal method for achieving universal, cost-efficient, and equitable scale-up remains unclear.

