### Randomization and Blinding

Given that CFHS clinicians may work across multiple CFHS within a region or sector, the randomization for this trial will be conducted at the CFHS sector level to minimize possible contamination across CFHS sites. The 6 CFHS sectors (including 39 CFHS) will be stratified by geographic location and number of births/year (based on whether the number of births is higher or lower than average), and randomized in a 1:1 ratio to one of the 2 trial arms (clinician-initiated or system-initiated). Randomization will occur by an independent statistician using Microsoft Excel. CFHS will not be blinded to group allocation; however, the primary trial outcome—reach and representativeness of HB4HNEKids—will be objectively assessed via electronic records of service enrollment.

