### Analysis

Analyses of trial outcomes will be undertaken under an intention-to-treat framework. For assessment of reach of HB4HNEKids—the primary trial outcome—between-group differences will be assessed using mixed logistic regression to account for any potential sector–level clustering effects. The regression model will include fixed effects for each arm of the trial and control for covariates prognostic of the outcome, including participant geographical location and ethnicity. To assess the impact of HB4HNEKids on child health behaviors, we will compare these outcomes between groups (clinician-initiated model vs system-initiated model) using mixed logistic and linear regression models. The model will include fixed effects for service and parent demographics that are found to be significantly different between scale-up models to account for potential consent bias. Subgroup analyses based on parent characteristics will also be conducted to examine differential effects on models of care against the outcome. We will use descriptive and comparative statistics to describe implementation and process outcomes, including engagement, acceptability, feasibility, appropriateness, and maintenance. All statistical tests will be 2-tailed with an α of .05.

Given that the trial is exploring the implications of the scale-up model (not the HB4HNEKids service), a data monitoring committee is not required for this trial. Data will be stored securely in accordance with the requirements of all ethics committees. Data will only be accessible to investigators listed on the ethics application and statisticians.

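### Six randomised sectors cannot give 80% power for a 9.8-point difference in reach at the plan's own ICC of 0.05

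*Protocol article*

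**What the plan says.** Under Sample Size and Power Calculation, the protocol article states that "a sample of 1126 participants or families per trial arm will enable a detectable difference of 9.8" percent, "assuming the opt-in model will achieve approximately 65% reach at 18 months", "with 80% power, α of .05, and an intraclass correlation coefficient of 0.05". It gives no number of clusters, cluster size or design effect, and does not say at which level the ICC applies.

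Under Randomization and Blinding, "the randomization for this trial will be conducted at the CFHS sector level to minimize possible contamination across CFHS sites". Six sectors containing 39 units are allocated 1:1, so there are three sectors per arm. The Analysis section plans a mixed logistic model for reach that allows for clustering by sector, and adds: "All statistical tests will be 2-tailed with an α of .05".

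The 65% is attributed to unpublished pilot data. The Introduction reports that the pilot "reached approximately 70% (6243/8501) of eligible parents".

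**The concern.** When whole sectors are randomised, the number of sectors limits the information in the trial. Three per arm is very few, and an ICC of 0.05 is large when each sector contributes hundreds of families. A detectable difference below 10 points looks out of reach under those conditions. The section's reassurance that the sample can be recruited concerns the number of families, which is not the limiting factor.

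The trial is meant to inform which enrolment model is scaled up. A team or reader relying on the stated power would expect the trial to find a 10-point difference in reach if one exists, and could give a non-significant result more weight than the design supports.

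**Working it through.** **Inputs.** 1126 per arm, 65% reach, a difference of 9.8 points (so 65% against 74.8%, opt-out being expected to do better), 80% power, ICC 0.05 (Sample Size and Power Calculation); two-sided 5% (Analysis); three sectors per arm (Randomization and Blinding). Equal sector sizes are assumed.

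**1. What the stated figures imply.** Without clustering, n per arm = (1.96 + 0.8416)² × (0.65×0.35 + 0.748×0.252) / 0.098² = 7.849 × 0.4160 / 0.009604 = 340, or 343 with pooled variance under the null. The implied design effect is 1126/343 = 3.28. From 1 + (m − 1)×0.05 = 3.28, m is about 47 families per cluster, and 1126/47 is about 24 clusters per arm. The trial has no such clusters.

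**2. The design as randomised.**
- Families per sector: 1126/3 = 375.3.
- Design effect: 1 + 374.3×0.05 = 19.7.
- Effective sample per arm: 1126/19.7 = 57.1.

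**3. Power for 9.8 points.** Standard error = √(0.4160/57.1) = 0.0854, and 0.098/0.0854 = 1.148. Normal approximation: Φ(1.148 − 1.96) = 0.21. Noncentral t with 6 − 2 = 4 df: 0.15. A beta-binomial simulation of 100,000 trials gave 20.9% and 15.1%.

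**4. Difference detectable with 80% power.** Solve d = c × √[(0.2275 + (0.65 + d)(0.35 − d))/57.1].
- Normal, c = 2.80: d = 0.217 (0.221 with pooled variance).
- t with 4 df, c about 3.76: d = 0.272.

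**5. More families.** The effective sample per arm is N/[1 + (N/3 − 1)×0.05], which approaches 3/0.05 = 60 as N grows. About 4,125 per arm is a derived assumption: 15,000 referrals in 18 months × 55% of births / 2. It gives an effective sample of 59.2 and a detectable difference of 21.4 points (normal) or 26.9 points (t). Reaching 343 effective families at ICC 0.05 needs more than 343×0.05 = 17.2 clusters, so at least 18 per arm.

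**6. Other readings of the stated figure.**
- 39 units as clusters (19.5 per arm on average): m = 57.7, design effect 3.84, effective sample 293. Power is 74% and the detectable difference 10.5 points (normal).
- No clustering: 1126 per arm would detect 5.5 points.
- A one-sided, continuity-corrected test on 39 units needs 1113 per arm. This comes close to 1126, but contradicts both the two-tailed testing and the sector randomisation.
- 9.8% as a relative difference is about 6.4 points (0.65×0.098), for which power is lower still.

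**7. Dependence on the sector ICC.** Detectable difference in points, normal / t with 4 df, by the formulas above:

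| Sector ICC | 1126 per arm | 4,125 per arm |
|---|---|---|
| 0.05 | 21.7 / 27.2 | 21.4 / 26.9 |
| 0.02 | 15.1 / 19.5 | 14.5 / 18.8 |
| 0.01 | 11.6 / 15.2 | 10.7 / 14.1 |
| 0.005 | 9.2 / 12.1 | 8.0 / 10.5 |

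At 1126 per arm, 9.8 points needs a sector ICC of about 0.006 (normal) or 0.002 (t).

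**8. Pilot reach.** 6243/8501 = 73.4%, against the assumed 65%. Starting from 73.4%, step 4 gives 19.1 (normal) or 23.6 points (t), so the conclusion does not depend on this input.

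**The case against.** The strongest objection is that the protocol does not say whether 0.05 is a between-sector or a between-unit ICC. If it is a unit-level value, 39 units with about 4,125 families per arm give a detectable difference of about 9.6 points (m = 211.5, design effect 11.5, effective sample 358), close to the stated one. The sector ICC could then be smaller, and the table shows how much that would help. This stands as a condition on the figure of 22 to 27 points. It does not rescue the statement: the article ties 9.8 points to 1126 per arm, where the unit-level reading gives 10.5, and units nested in randomised sectors are not independent clusters.

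Second, the article fixes no degrees-of-freedom method, and such detail is commonly left to the analysis plan. Stratification and covariates might remove some between-sector variance, though they can also use up degrees of freedom. That is a reason to report the range and not only its upper end. The power statement itself claims no such gain.

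Third, a non-significant result should be read from its confidence interval, and the true contrast may be large. Both are fair. For 65% against 95%, power at 1126 per arm is about 99% (normal) or 89% (t). The trial can detect a large contrast, but not the one it states.

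Fourth, the 65% and the 73.4% may be different quantities, since the Introduction gives no time point for the pilot figure. That is possible, so this part is only a request to explain.

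**Conclusion.** The power statement is wrong as written. At the protocol's own ICC, with three sectors per arm and 1126 families per arm, power for 9.8 points is about 15% to 21%, not 80%. The detectable difference is about 22 to 27 points, more than twice the stated one. This assumes that the ICC of 0.05 applies between sectors, that sectors are equal in size, that opt-out has the higher reach, and that covariates explain no between-sector variance. Unequal sectors would lower power, as would a difference in the other direction (65% against 55.2%: power 13% to 19%). A sector ICC well below 0.05 would raise it, but at 1126 per arm it would have to be roughly one-eighth to one-twenty-fifth of the stated value. The pilot discrepancy is secondary and does not affect this conclusion.

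**What to change.** Recalculate and rewrite the Sample Size and Power Calculation section for the trial as randomised: three sectors per arm, all eligible families, the design effect shown, and the level of the ICC named. At ICC 0.05, report a detectable difference of about 21 to 27 points with the full eligible sample, making clear that the upper end uses a t reference with 4 df, and report about 15% to 21% power for 9.8 points. Add a short table over sector ICCs from 0.005 to 0.05. If a smaller sector ICC is believed, estimate it from existing service or pilot records and recompute. Either explain why 65% was chosen over the pilot's 73.4% or use one figure throughout. Log the change in the trial registration, as the article already promises for modifications.

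The cost is a recalculation and rewording. No families, sectors or procedures change. The price is a much less favourable statement of what the trial can detect.

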### Analysis

Analyses of trial outcomes will be undertaken under an intention-to-treat framework. For assessment of reach of HB4HNEKids—the primary trial outcome—between-group differences will be assessed using mixed logistic regression to account for any potential sector–level clustering effects. The regression model will include fixed effects for each arm of the trial and control for covariates prognostic of the outcome, including participant geographical location and ethnicity. To assess the impact of HB4HNEKids on child health behaviors, we will compare these outcomes between groups (clinician-initiated model vs system-initiated model) using mixed logistic and linear regression models. The model will include fixed effects for service and parent demographics that are found to be significantly different between scale-up models to account for potential consent bias. Subgroup analyses based on parent characteristics will also be conducted to examine differential effects on models of care against the outcome. We will use descriptive and comparative statistics to describe implementation and process outcomes, including engagement, acceptability, feasibility, appropriateness, and maintenance. All statistical tests will be 2-tailed with an α of .05.

Given that the trial is exploring the implications of the scale-up model (not the HB4HNEKids service), a data monitoring committee is not required for this trial. Data will be stored securely in accordance with the requirements of all ethics committees. Data will only be accessible to investigators listed on the ethics application and statisticians.

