**Methods:**

A randomized controlled trial will be conducted in 6 Child and Family Health Service (CFHS) sectors (39 CFHS units) within the Hunter New England region of New South Wales, Australia. The 6 CFHS sectors will be randomized in a 1:1 ratio to one of 2 arms, stratified by sector location and average number of births per annum. The intervention arm (a clinician-initiated opt-in model of care) will involve a series of implementation support strategies delivered to CFHS staff (ie, training, audit, and feedback) to support clinicians in connecting eligible families to the HB4HNEKids program. The control arm (a system-initiated opt-out model of care) will use existing health service data to identify participants meeting the predefined eligibility criteria to automatically initiate the commencement of HB4HNEKids messages to families (ie, will not require input from CFHS staff). The primary outcome will assess the reach and representativeness of participants receiving HB4HNEKids. Secondary outcomes will include child health behaviors (breastfeeding rates; age of introduction to solids; child fruit, vegetable, and discretionary food intakes; as well as child immunization rates) captured via parent survey, as well as the cost-effectiveness.

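### The primary test of reach rests on six randomized sectors with no small-sample method named; standard large-sample inference would give a false-positive rate of about 12-19% rather than 5%

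*Protocol article*

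**What the plan says.** Under Randomization and Blinding, the protocol article states that "the randomization for this trial will be conducted at the CFHS sector level". It adds that "The 6 CFHS sectors (including 39 CFHS) will be stratified by geographic location and number of births/year" and then "randomized in a 1:1 ratio to one of the 2 trial arms". That gives three sectors per arm, with the 39 units nested inside them.

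For the primary comparison of reach, the Analysis section states that "between-group differences will be assessed using mixed logistic regression to account for any potential" clustering by sector. The model has a fixed effect for arm and will "control for covariates prognostic of the outcome, including participant geographical location and ethnicity". The same section closes the inferential rules with "All statistical tests will be 2-tailed with an α of .05".

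The article does not say whether the arm effect is tested by Wald z, likelihood ratio or t. It gives no estimation method (ML or REML-type), degrees of freedom or small-sample correction. The Sample Size and Power Calculation section assumes an ICC of 0.05, 65% reach under opt-in, a 9.8% detectable difference, 80% power and 1126 families per arm.

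**The concern.** Standard inference from a logistic mixed model is a large-sample method in the number of clusters. Arm varies only between sectors, so its precision depends on a between-sector variance estimated from six values with 4 df. ML biases that variance downward. A normal or chi-square reference then ignores the uncertainty in it. Enrolling more families per sector does not change the number of sectors.

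If the stated model is fitted with ordinary software defaults, the interval for the trial's main answer is too narrow, and a true null is rejected well over twice as often as the stated α allows. That answer is meant to guide a choice between two ways of scaling up a population-wide service.

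**Working it through.** **Inputs.** Six sectors, 3 v 3, are from Randomization and Blinding. Two-sided α of .05 is from Analysis. ICC 0.05, 65% reach, 9.8 points and 1126 per arm are from Sample Size and Power Calculation. Sector sizes are not given. I assume 1126/3 ≈ 375. As a larger case I use 15,000 × 0.55/6 = 1375, from the expected 18-month referrals and the stated 55% share of births.

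**The plan's own figure.** Without clustering, 65% v 74.8% needs 343 per arm. So 1126 implies a design effect of 1126/343 = 3.28, or 1 + (3.28 − 1)/0.05 ≈ 47 families per cluster. With three sectors per arm the design effect is 1 + (375.3 − 1) × 0.05 = 19.7, and the effective sample is 1126/19.7 ≈ 57 per arm. I could not reproduce 1126 with either the 6 sectors or the 39 units as clusters.

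**Closed form.** For large, equal sectors, let T be the ordinary two-sample t statistic on six sector values, with 4 df under the null.

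- ML Wald z: ML divides the residual sum of squares by 6 rather than 4, so the test rejects when |T| > 1.96 × √(4/6) = 1.600. P = 18.5%.
- Likelihood ratio: 6 ln(1 + T²/4) > 3.84, so |T| > √(4(e^(3.84/6) − 1)) = 1.894. P = 13.1%.
- REML-type z: |T| > 1.96. P = 12.2%.
- ML standard error with a t4 reference: |T| > 2.776 × √(4/6) = 2.267. P = 8.6%.
- REML-type with a t4 reference: |T| > 2.776. P = 5.0%.

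If one sector-level covariate is fitted, 3 df remain. The uncorrected rates become about 14% (REML-type z), 20% (likelihood ratio) and 26% (ML Wald z).

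**Simulation under no arm effect.** 65% reach, normal sector effects on the logit scale, no covariates, 2000 replicates per case, Monte Carlo standard error about 0.8 points:

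| Families per sector, ICC | ML Wald z | Likelihood ratio | ML with t4 | Sector-level t-test |
|---|---|---|---|---|
| 375, .05 | 18.0% | 12.8% | 8.1% | 5.3% |
| 1375, .05 | 17.9% | 12.7% | 8.6% | 5.4% |
| unequal 150-700, .05 | 17.4% | 13.1% | 8.8% | 5.3% |
| 375, .01 | 16.6% | 11.9% | 6.5% | 4.9% |
| 375, .10 | 18.4% | 13.0% | 8.6% | 5.2% |
| 375, .001 | 9.0% | 7.0% | 1.5% | 5.5% |

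A second simulation, with beta-binomial sector proportions and ICC .01 or .05, gave 15.8-19.3% for ML Wald z, 7-10% for ML with t4, and 4.5-6.7% for the sector-level t-test.

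**Interval width.** The t4 multiplier is 2.776 against 1.96, so a z interval with an unbiased variance should be 1.42 times wider. With the ML variance the factor is 1.42 × √(6/4) = 1.73.

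**Power of a valid test.** The standard error of the difference is √(19.7 × (0.65 × 0.35 + 0.748 × 0.252)/1126) = 0.0853. The noncentrality is 0.098/0.0853 = 1.15, and a two-sided t-test on 4 df then has about 15% power.

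**The case against.** The strongest reply is that the article names a model class and nothing more. ML, a Wald z statistic and a normal reference appear nowhere in it. Such details are often left to an analysis plan, which is not shown and might specify a correction. This stands as a limit on the claim: the absence of a small-sample method is established for the article only. It does not remove the point. The article fixes six clusters, a model and an α that do not fit together unless a correction is added. Its sample-size figure also implies clusters of about 47 families, so it does not reckon with six sectors.

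Some stronger readings are tempting and are not supported:

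- **A flat false-positive rate of 16-19%.** That range belongs to the ML Wald z test at ICC .01-.10, and the protocol does not commit to that test.
- **A mixed model is invalid here.** It is not: by the closed form, a REML-type fit with a t4 reference holds 5.0%.
- **Opt-out sectors will sit near a ceiling, so a common sector variance must fail.** The design's own figures, 65% plus 9.8 points, put reach near 75%. The pooled t-test also assumes a common variance: if one arm's sector variance were near zero it would behave like t on 2 df and reject at P(|t2| > 2.776) = 10.9%. This is a matter for sensitivity analysis.
- **A logistic model clashes with a percentage-point target.** A percentage-point difference can be derived from a logistic fit, and the article does not say how the effect will be reported.
- **The child-behaviour models share the same inflation.** They were not simulated, and the article gives no ICC for those outcomes.

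**Conclusion.** The point holds for the primary test of reach. With six sectors and standard large-sample inference, the nominal 5% test has a true false-positive rate of about 12-19% for ICC .01-.10, which includes the protocol's own value of .05. The rate depends on the test: about 17-18% for ML Wald z, and 12-13% for the likelihood ratio test or REML-type z. At an ICC near .001 it is 7-9%. Confidence intervals are too narrow by a factor of about 1.4 to 1.7.

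These figures assume a common sector variance, the sector sizes stated above and no covariates in the simulated model. Using location as a sector-level covariate would raise the uncorrected rates. The conclusion does not depend on enrolment, because more families leave the number of sectors unchanged.

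**What to change.** State in the analysis plan that the primary inference on reach uses the six sectors with 4 df, reduced by one for each sector-level covariate fitted. Either of two routes would serve:

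1. A two-stage analysis: fit an individual-level logistic model with the planned covariates but without arm, obtain adjusted reach for each sector, and compare three v three by t-test. Report the percentage-point difference with its t-based confidence interval.
2. A REML-type mixed model with a named small-sample df correction.

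An uncorrected ML fit should not carry the primary conclusion, and a t4 reference on an ML fit is not enough (about 7-10% at ICC .01-.05 in the second simulation above). Add a sensitivity analysis that allows sector variance to differ between arms. Do not rely on a permutation test: choosing 3 of 6 sectors gives 20 allocations, so the smallest two-sided p is 2/20 = 0.10, and larger under the stratified allocation.

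The drafting cost is a paragraph and a few lines of code. The statistical cost is wider intervals and low power, about 15% for 9.8 points at ICC .05 with about 375 families per sector (assumed from 1126 per arm). The Sample Size and Power Calculation section must therefore be restated for six randomized sectors.

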### Data Collection Procedures and Measures: Primary Outcome

The primary trial outcome will be the reach and representativeness of the HB4HNEKids program at 4, 6, 12, and 18 months from the commencement of the scale-up phase. The reach of the program by the scale-up model (clinician-initiated vs system-initiated) will be explored. Reach will be defined as: the number of eligible parents that are receiving HB4HNEKids (assessed via project records) and the proportion of parents receiving the program, calculated by the number of eligible parents receiving HB4HNEKids (numerator), divided by the total number of parents eligible for the program (denominator), identified via electronic health service records.

Representativeness will be assessed by comparing the characteristics of the parents receiving HB4HNEKids via each scale-up model to those of the total sample of eligible parents or carers referred to CFHS during the 18-month trial period. Characteristics of eligible parents (collected via electronic health service records and “The Good for Kids Parent Collective”) include parental age, geographic location, highest level of education, employment status (before birth of child), first baby (yes or no), number of children, language spoken at home other than English, and Aboriginal and Torres Strait Islander status. Sample representativeness of parents receiving the HB4HNEKids program at baseline and those remaining engaged at 18 months from both scale-up models will be compared, as well as compared with characteristics representative of the wider Hunter New England population.

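### Covariates for the secondary child-behaviour models are chosen by significant between-arm difference, a rule that ignores prognosis and does not reliably deal with consent bias

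*Protocol article*

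**What the plan says.** The Analysis section gives two different covariate rules. For reach, the primary outcome, the model will "control for covariates prognostic of the outcome, including participant geographical location and ethnicity". For the child-behaviour outcomes, the mixed models will contain "fixed effects for service and parent demographics that are found to be significantly different between scale-up models to account for potential consent bias". The section sets the general test level ("All statistical tests will be 2-tailed with an α of .05"). It does not say which test compares the demographics, or whether that test allows for clustering.

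Other sections bear on this:

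- Randomization and Blinding: "The 6 CFHS sectors (including 39 CFHS) will be stratified by geographic location and number of births/year", allocated 1:1, so three sectors per arm.
- Child Health Behaviors: the surveys go to families receiving the program.
- Ethical Considerations: completing the survey counts as consent.
- Data Collection Procedures and Measures: Primary Outcome: the recorded characteristics "include parental age, geographic location, highest level of education, employment status (before birth of child), first baby (yes or no"), and also number of children, language at home, and Aboriginal and Torres Strait Islander status. That makes eight candidates.

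**The concern.** A covariate distorts an arm comparison through two things together: its imbalance and its association with the outcome. The stated rule looks only at the first, and only through a p-value, which also depends on sample size. A strong predictor with a moderate but non-significant imbalance is left out, while a variable unrelated to feeding or diet can enter. The reach model in the same section avoids this by choosing covariates for prognosis. No reason is given for the different rule in the behaviour models, where selection is the greater worry.

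The rule's stated purpose is consent bias. That bias arises after randomisation, in two steps: who comes to receive the program (offered by a clinician in one arm, automatic in the other) and who then answers the survey. A test between arms examines neither step directly.

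The article hypothesises that the opt-in model will do more for health behaviours. These models test that hypothesis, so a data-dependent adjustment set leaves the estimate open to challenge.

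**Working it through.** **Plan's own figure.** The plan gives none for this point. Its one computed design figure ("a sample of 1126 participants or families per trial arm will enable a detectable difference of 9.8" percentage points) concerns reach. Below, 1126 serves only as an upper scale for respondents per arm, and the argument does not depend on it.

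**Inputs.** From the article: six sectors, three per arm, α = 0.05 two-sided, eight candidate characteristics. Assumed, because the article does not give them: 300 or 1126 survey respondents per arm, and a covariate intraclass correlation (ICC) of 0.01 to 0.05. The article's ICC of 0.05 is for reach, not for demographics. Sectors are taken as equal in size. The stratified allocation is ignored; it could lower the rates for variables that track location or birth numbers.

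**If the test is at individual level.** With m = n/3 respondents per sector, the design effect is DE = 1 + (m − 1) × ICC. The chance of flagging a variable with no systematic arm difference is 2 × [1 − Φ(1.96/√DE)].

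| n per arm | m | ICC | DE | Flag rate |
|---|---|---|---|---|
| 300 | 100 | 0.01 | 1.99 | 17% |
| 300 | 100 | 0.02 | 2.98 | 26% |
| 300 | 100 | 0.05 | 5.95 | 42% |
| 1126 | 375.3 | 0.01 | 4.74 | 37% |
| 1126 | 375.3 | 0.02 | 8.49 | 50% |
| 1126 | 375.3 | 0.05 | 19.72 | 66% |

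Example: DE = 1 + 374.33 × 0.01 = 4.74; 1.96/√4.74 = 0.90; rate 37%. A beta-binomial simulation (20,000 runs, prevalence 30%, m = 100 and 375) agrees to within about one percentage point.

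**If the test is at sector level.** In the same simulation, a t-test on three against three sector proportions holds about 5%. With 375 respondents per sector, it detects a true imbalance of 30% against 40% in only 42%, 27% and 15% of trials at ICC 0.01, 0.02 and 0.05.

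**Multiplicity.** Even with no clustering, eight independent tests give 1 − 0.95⁸ = 34% chance of at least one false flag.

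**Consent bias, one constructed example with no true arm effect.** A measured demographic (prevalence 40%) and an unmeasured trait both predict the outcome. Survey response depends on the trait, more strongly in the opt-in arm (log-odds slope 0.8 against 0.2). Among responders:

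- The demographic is balanced, 39.8% against 39.8%, so the rule would not select it.
- The outcome nevertheless differs, 54.5% against 50.0%, or 4.4 points from unrounded values.
- Within levels of the demographic the gap is still 3.9 to 4.8 points.

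This shows that the mechanism is possible; it does not estimate its size in this trial.

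**The case against.** Several objections carry weight.

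- *The flag rates rest on an unstated test.* The outcome models are mixed models, so the demographic comparison may also respect clustering, and the false-flag rate would then be 5%. This stands: the 17% to 66% range is conditional. It does not rescue the rule, because the sector-level alternative misses most real imbalances.
- *A flag is not harm.* A reader might infer that the rule picks up sector clustering rather than confounding. The documents do not support that contrast. With three sectors per arm, a chance sector imbalance in a prognostic variable is confounding in the realised sample, and adjusting for it helps. The flag rate shows how haphazard the selection is, not how biased the result is.
- *Over-flagging and serious omission do not occur together.* Under an individual-level test at 1126 per arm, an unflagged variable with assumed 30% prevalence differs by less than 1.96 × √(2 × 0.21/1126) = 3.8 points. If it shifts the outcome by an assumed 20 points, the bias left is under 0.8 points. At 300 per arm the limits are 7.3 and 1.5 points. This stands: sizeable omissions belong mainly to the sector-level reading.
- *The rule does something about consent bias.* Adjustment removes the part carried by the demographics it selects. It would be too strong to say the rule does not correct consent bias at all.
- *Changing sets by age.* The article does not say the test is repeated at each survey age, so it cannot be asserted that the covariate set will differ between ages.

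**Conclusion.** The point holds for the secondary child-behaviour models. The article states a selection rule, rather than leaving it to an analysis plan, and the rule uses the wrong criterion. It ignores prognosis and departs from the approach taken for reach in the same section. Under either reading of the test, it is a poor guide with six sectors. It does not reliably correct consent bias, because it never compares respondents with eligible non-respondents.

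The percentages are illustrations over assumed ICCs and respondent numbers, not properties of this trial. No bias in the behaviour estimates has been quantified for the trial itself. A reader might extend the point to the main result, but the reach model selects covariates for prognosis, so the primary analysis is untouched. The change should be made; the trial's main conclusion does not depend on it.

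**What to change.** Remove the significance condition. Name in advance one short set of prognostic covariates for every behaviour outcome and age, to be used whatever imbalance is observed. Parental age, education, first baby, language at home, Aboriginal and Torres Strait Islander status and geographic location are candidates already listed in the article, and this matches the approach for reach. Keep sector-level terms to a minimum, since six sectors support very few. Decide in advance whether the births-per-year stratification factor is one of them.

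Treat response as a separate sensitivity analysis. Compare respondents with all eligible families, and weight respondents on whichever predictors the electronic records hold for both.

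The cost is new wording, logged in the trial registration as the article provides for changes, and a little more analysis. The weighting has a limit. The article draws the characteristics from health records and the Parent Collective together, without saying which source supplies which. Education or employment may therefore be unavailable for families who did not respond. The wording should be settled before behaviour outcomes are compared by arm.
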